## Background

Functional constipation is a common disease, both in adults and in children. The prevalence in children ranges from 0.7% to 29.6%. In adults, functional constipation affects between 0.7% and 79% of the general population [1]. The prevalence is higher in females, older individuals, those of lower socioeconomic status, and those with a lower educational level [2,3]. As a common and well-recognized public health problem, functional constipation influences patient quality of life and consumes many healthcare resources [4,5].

Several therapies (such as lifestyle changes, osmotic agents, bulking agents, and so on) [6,7] have been used in clinical practice, which is believed to be helpful in relieving symptoms. Nonetheless, many of these therapies were not proven to be effective for the condition, or were difficult to tolerate because of adverse events [8-10].

Because of the unclear etiology and pathogenesis, the therapeutic options are relatively limited. As a result, complementary or alternative therapies, such as acupuncture, are attractive to both patients and practitioners. China has a long history of managing gastrointestinal symptoms through acupuncture, including diarrhea, constipation and gastroenteritis [11]. Results of several randomized controlled trials (RCTs) showed that acupuncture may be an effective treatment for functional constipation, by improving frequency and time of defecation, and the patient’s quality of life [12-14]. However, convincing evidence for the effectiveness of treating functional constipation with acupuncture is still inadequate, due to the poor quality of current studies. Therefore, we designed a multicenter randomized controlled trial to address these problems and hopefully provide a more conclusive answer to the questions.

In this trial, we first aim at investigating whether acupuncture is effective in treating functional constipation through a comparison with Mosapride Citrate control. Second, we will attempt to determine whether different acupuncture points are the same in managing this condition. The work reported in this article is financed by the National Basic Research Program (973 Program) in China, and is registered with an identifier (NCT01411501) in Clinical Trials.gov.

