### Interventions and comparison

#### Rationale for acupuncture protocol

The acupuncture protocol in this trial was formed in two steps: first, we screen for a range of acupuncture points and stimulation methods through a systematic review of records of ancient books and acupuncture textbooks, as well as results of published articles; second, meetings were held to further screen for a standardized acupuncture protocol and reach consensus among acupuncture experts in China. Based on the theory of acupuncture and TCM, Back-Shu and Front-Mu points (short for Shu-Mu points) are the classic combination for the treatment of internal organ disease, which is located in the abdomen or lower back of the body, so Back-Shu and Front-Mu acupuncture points of Large Intestine meridians are supposed to be the best points prescription to treat Large Intestine disease. Additionally, He-Sea and Lower He-Sea acupuncture points of Large Intestine meridians are also positive points prescription, which is situated in the upper or lower limbs of the body, as stated: ’He points are the best points to treat internal organ’s disease’ in *Nei Jing*. In our hypothesis, the combination of Shu-Mu points and He-sea points will achieve better therapeutic outcomes, and all the acupuncture groups will be non-inferior to Mosapride Citrate. Therefore, groups in our trial are defined as: (1) Back-Shu and Front-Mu acupoints of Large Intestine meridians (Shu-Mu points) group; (2) He-Sea and Lower He-Sea acupoints of Large Intestine meridians (He points) group; (3) Combining used Back-Shu, Front-Mu, He-Sea, and Lower He-Sea acupoints of Large Intestine meridians (Shu-Mu-He points) group; and (4) Mosapride Citrate control group (Table 1).

**Table 1 T1:** Details of acupuncture protocol

**Group names**	**Acupuncture points**	**De qi sensation**	**Stimulation**
Back-Shu and Front-Mu acupoints of Large Intestine meridians (Shu-Mu points group)	Tianshu (ST25) Dachangshu (BL25)	Yes	Both points are punctured bilaterally. Tianshu (ST25) is punctured perpendicularly 1–1.5 cun. Dachangshu (BL25) is punctured perpendicularly 0.8-1.2 cun
He-Sea and Lower He-Sea acupoints of Large Intestine meridians (He points group)	Quchi (LI11) Shangjuxu (ST37)	Yes	Both points are punctured bilaterally. Quchi (LI11) is punctured perpendicularly 0.5-1 cun. Shangjuxu (ST37) is punctured perpendicularly 1–2 cun

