### Sample size calculation and statistical analysis

According to the previous literature [16], an improvement of 2.6 times (standard deviation 2.4) for defecating during 1 week with functional constipation by prucalopride is reported, and a difference of 1.6 times between groups is considered to be of clinical relevance [16]. In this study, we anticipated an improvement of 4.0 times by Shu-Mu points group, 3.8 times by He points group, 5.2 times by Shu-Mu-He points group, and 2.6 times by Mosapride Citrate tablet group. A standard deviation of 6.0 is considered, to allow a relatively high heterogeneous variance in this population. Moreover, we mainly focus on the comparison of Shu-Mu-He points group *vs*. Mosapride Citrate tablet group. So the between-group comparison will be done as: first, Shu-Mu-He points group will be compared with Mosapride Citrate tablet group as the primary comparison, since the prescription of Shu-Mu-He points is considered to be better than the other two acupuncture protocols; second, comparisons among acupuncture groups will be performed also as exploratory analysis. So, we used GPower 3.1.3 [Franz Faul, Universität Kiel, Germany], and input the four group mean defecation rates as 4.0, 3.8, 5.2, and 2.6 per week, with a common assumed standard deviation of 6.0, giving a calculated effect size of 0.15. With four groups of equal size (175/group, 700 in total) this gives the study 90% power at a 5% level of significance to detect such an overall effect size using a one-way ANOVA fixed effects omnibus test, and assuming a 15% loss to follow-up. For the pairwise comparison of primary interest (Shu-Mu-He *vs*. mosapride citrate) the study has over 90% power at a 1% level of significance (to make some adjustment for multiple comparisons) to detect a mean difference of 2.6 (5.2 to 2.6) assuming the common standard deviation of 6.0 defecations with 175 participants per group.

Statistical analysis will be performed by the Clinical Evaluation Center of China Academy of Chinese Medical Sciences in Beijing. The statistician is blinded from the allocation of groups. SPSS13.0 and SAS9.0 statistical software packages will be used to analyze the data.

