Prior to all analyses, a detailed statistical analysis protocol was developed. The intention-to-treat (ITT) population was defined as the patients who are randomized and received at least one treatment session. The per-protocol (PP) population was defined as the patients who completed the study and do not have major protocol violations. All analyses were based on the ITT population and PP population. And the result of the ITT analysis will be compared with that of the PP analysis to check whether the results are consistent.

First of all, baseline characteristics will be analyzed by descriptive statistics for each group. Then analysis is done to make comparisons among the treatment groups and control group. If a significant difference is found by comparison of the treatment groups and the control group, the next step is to make comparisons among three acupuncture points treatment groups in effectiveness. Multiple comparisons will be adjusted according to Bonferroni correction method.

The repeated measures analysis will be used in the different time points assessment. The Kruskal-Wallis test will be employed in the analysis of skewed distribution data. Analysis of variance (ANOVA) is used for numerical variables, and Chi-square test for categorical variables.

There is one acupuncturist in each center to do all three interventions, which probably introduces clustering effect in this trial. Therefore, we calculated the intracluster correlation coefficient from the results of this trial and report the coefficient [17].

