A major issue in planning the design of this trial is whether sham acupuncture should be used. Since the primary consideration of this trial is to clarify whether acupuncture is effective or whether acupuncture helps relieving symptoms of patients with functional constipation, we all agree that a pragmatic design is more suitable, which requires a positive drug as the control group. There is some evidence that Mosapride is effective for improvement of lower tract mobility, and thus is effective for management of constipation [18-20]. However, there is no proven drug clearly ahead of the rest. We choose Mosapride as a positive drug control based on: (1) it was reported to be superior to placebo for irritable bowel syndrome (IBS) patients with constipation, and it may have the potential to treat IBS patients with constipation and/or functional constipation [21]; and (2) a randomized controlled trial in China showed the same result [22], which indicates Mosapride may be a better option than other medication for Chinese population with functional constipation. So we choose Mosapride Citrate as a positive drug control. In this trial, we did not include a placebo acupuncture control, because we did not know whether acupuncture is effective for patients with functional constipation. Thus, if acupuncture is effective, then the next step would be to compare acupuncture with sham acupuncture to clarify absolute acupuncture treatment effect.

There are three different acupuncture groups in this trial, which are all expected to be effective according to traditional acupuncture theories. Combined use of Back-Shu and Front-Mu (Shu-Mu points) are regarded as the most commonly acupuncture prescription. In addition, He-Sea and Lower He-Sea points of Large Intestine meridians are also commonly used acupuncture prescription. The prescription of Shu-Mu-He points is composed of both Shu-Mu points (Shu-Mu points group, located at abdomen and lower-back) and He points (He points group, located at upper and lower limbs), which is expected to be the best therapeutic effect. Comparison of the three acupuncture groups will solve the question: whether combined use of Shu-Mu-He points will lead to better clinical outcome than using Shu-Mu or He points alone, which may give insights to whether traditional acupuncture theories work.

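### The comparisons among the three acupuncture groups are conditional on a significant result against mosapride in one place and unconditional in three others; the condition can leave the second aim unanalysed

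*Protocol article*

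**What the plan says.** The section on sample size and statistical analysis speaks twice about comparing the acupuncture groups with each other. The sample-size paragraph sets an order: "first, Shu-Mu-He points group will be compared with Mosapride Citrate tablet group as the primary comparison", and then "second, comparisons among acupuncture groups will be performed also as exploratory analysis". It attaches no condition to the second step. The later analysis text does attach one: "If a significant difference is found by comparison of the treatment groups and the control group, the next step is to make comparisons", where the next step is "comparisons among three acupuncture points treatment groups in effectiveness". It does not say which test of treatment against control is meant, at what level, or in which direction. It adds that multiple comparisons are Bonferroni-adjusted.

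Elsewhere the question is unconditional. The Background gives it as the second aim: "Second, we will attempt to determine whether different acupuncture points are the same in managing this condition". The Discussions section says "Comparison of the three acupuncture groups will solve the question" of whether the combination does better than either component set. The rationale for the acupuncture protocol hypothesises that "all the acupuncture groups will be non-inferior to Mosapride Citrate".

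**The concern.** After a non-significant result against mosapride, one sentence says the prescriptions are not compared and another says they are. A reader of the eventual report could not tell which rule applied, and the choice could be made after the results are known.

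The condition also has no logical link to the question it controls. A difference between Shu-Mu, He and Shu-Mu-He is a contrast among three arms that does not involve mosapride's mean. If acupuncture performs about as well as mosapride, that agrees with the non-inferiority hypothesis, yet most versions of the gate would then usually stay shut. Because no direction is given, the gate would also open if acupuncture were significantly worse.

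**Working it through.** **Inputs from the sample-size paragraph.** The authors "input the four group mean defecation rates as 4.0, 3.8, 5.2, and 2.6 per week" (Shu-Mu, He, Shu-Mu-He, mosapride), with SD 6.0, 175 per arm and 15% loss. Evaluable per arm: 175 × 0.85 = 148.75, taken as 149.

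**Assumptions added here.** Normal outcome, two-sided tests, Bonferroni over three acupuncture pairs (0.05/3 = 0.0167), and an alternative scenario in which mosapride equals the acupuncture average: (4.0 + 3.8 + 5.2)/3 = 4.33.

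**1. The plan's own figures.** Deviations of the planned means from 3.9 are 0.1, −0.1, 1.3 and −1.3. Their root mean square is √(3.40/4) = 0.922, so f = 0.922/6.0 = 0.154. The four-group F test at 5% then has 94.0% power with 175 per arm and 89.6% with 149 (stated: 90%). For Shu-Mu-He against mosapride with 175 per arm, SE = 6.0 × √(2/175) = 0.641 and 2.6/0.641 = 4.05. Power at 1% is about Φ(4.05 − 2.58) = 93% (stated: over 90%). Both figures reproduce.

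**2. How often the gate opens.** The text names no test, so the plausible ones are taken in turn, with 149 per arm and SE = 6.0 × √(2/149) = 0.695. In the alternative scenario:

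- Shu-Mu-He against mosapride: (5.2 − 4.33)/0.695 = 1.25. Power is Φ(1.25 − 1.96) = 24% at 5% and Φ(1.25 − 2.58) = 9% at 1%.
- Four-group F test: deviations −0.33, −0.53, 0.87 and 0 have mean square 0.287, so the noncentrality is 596 × 0.287/36 = 4.7 and power is 42%.
- Pooled acupuncture against mosapride: the true difference is zero, so the gate opens at its level, 5%.
- Any of three pairs, Bonferroni: 20% by simulation.

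**3. What the gate costs.** Without a gate, the chance that at least one acupuncture pair is significant is 45% (simulation), wherever mosapride lies. With a gate, a detection also needs the gate to open:

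| Gate | Opens, mosapride 4.33 | Any acupuncture pair detected (ungated 45%) |
|---|---|---|
| Pooled acupuncture vs mosapride, 5% | 5% | 2% |
| Shu-Mu-He vs mosapride, 1% | 9% | 8% |
| Shu-Mu-He vs mosapride, 5% | 24% | 18% |
| Any of three, Bonferroni | 20% | 16% |
| Four-group F test, 5% | 42% | 38% |

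The pooled row can be checked by hand. The pooled contrast is essentially independent of the contrasts among the acupuncture arms, so 0.05 × 0.45 = 0.02. The F test loses least because it also responds to differences among the acupuncture arms.

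**4. Under the planned means** (mosapride 2.6), these five gates open in 86% to 96% of trials. For the pooled gate, detection is 0.86 × 0.45 = 39% against 45%. A gate requiring all three arms to beat mosapride would open in only 29%.

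**5. Is the gate needed for error control?** With three equal acupuncture arms and no gate, Bonferroni over three holds the family-wise error at 4.4%. It is not needed.

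**6. Power once the gate is removed**, at 0.0167 (critical value about 2.40):

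- Shu-Mu-He vs Shu-Mu (1.2): 1.2/0.695 = 1.73, power 25%; with 175 per arm 1.2/0.641 = 1.87, power 30%.
- Shu-Mu-He vs He (1.4): 2.01, power 35%; with 175 per arm 2.18, power 41%.

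**The case against.** Asking which prescription is best only after acupuncture has been shown to differ from the control is a common sequential strategy. The plan puts its main weight on Shu-Mu-He against mosapride and calls the other comparisons exploratory. The sample size rests on a four-group ANOVA, so an omnibus test followed by pairwise tests is a fair reading, and that version costs little (45% to 38%). Under the planned means almost any version opens. A separate analysis plan, not shown, may name the test. All of this stands and limits the size of the point. It does not make the two sentences in one section agree, or fit the condition to an aim stated without one.

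A reader might go further and infer that the gate biases the comparison towards the combination, because the Shu-Mu-He mean is reused after being selected for being high. The text does not support this in general, since it refers to the treatment groups together and does not name Shu-Mu-He against mosapride as the gate. When the acupuncture arms are equal, the bias is zero for a pooled, omnibus or any-of-three gate. Under the planned means a Shu-Mu-He gate gives at most about 0.08 defecations per week, and a gate requiring all three arms gives a negative bias. A larger figure, roughly 0.26 (5% gate) or 0.41 (1% gate), needs a Shu-Mu-He gate together with acupuncture arms all equal to 4.0 and mosapride at 2.6. The matching one-sided false-positive rates of 4.4% and 6.6%, against a nominal 2.5%, are conditional on an open gate and ignore the Bonferroni adjustment. Unconditionally they are 2.3% and 1.9%, so the gate does not raise the error rate.

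**Conclusion.** The point holds as an inconsistency and a poorly chosen precondition. The condition in the analysis text conflicts with the sample-size paragraph, the second aim in the Background and the claim in the Discussions section. It can leave that aim unanalysed after a result that agrees with the non-inferiority hypothesis.

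The size is conditional. If mosapride does as well as the average acupuncture arm, the five gates examined open in 5% to 42% of trials, and the chance of detecting any acupuncture difference drops from 45% to between 2% and 38%. If the planned means hold, the loss is small for those gates. These figures rest on SD 6.0, 149 evaluable per arm, normal outcomes, two-sided tests, Bonferroni over three, and an assumed mosapride mean of 4.33 that is not in the plan.

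It would be too strong to say that the second aim is bound to be lost: the sample-size paragraph still plans the comparisons, and the gate usually opens under the planned means. A general bias towards the combination is not established either.

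**What to change.** Delete the precondition in the analysis text and align it with the sample-size paragraph. State that the comparisons among the three acupuncture groups will be reported as exploratory estimates with confidence intervals, with the Bonferroni adjustment already stated, whatever the result against mosapride. If a condition is kept on purpose, name its test, level and direction, and change the Background, the sample-size paragraph and the Discussions section to match.

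The cost is one sentence, with no change to data, visits or sample size. It should be settled before group results are seen. Removing the gate does not make the second aim well powered: at 25% to 41% per pair involving Shu-Mu-He, a non-significant difference should not be read as showing that the prescriptions are the same, and the Discussions section should not promise that the comparison will settle the matter.

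### Plain Bonferroni is valid but needlessly conservative: Holm, with Shaffer's version among the three acupuncture groups, holds the same family-wise error and rejects more

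*Protocol article*

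**What the plan says.** All of this is in the article's section on sample size calculation and statistical analysis, except where noted.

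- **Adjustment:** "Multiple comparisons will be adjusted according to Bonferroni correction method". No step-down or closed procedure is mentioned, and the number of comparisons covered is not given.
- **Order:** "If a significant difference is found by comparison of the treatment groups and the control group, the next step is to make comparisons among three". The three in question are the acupuncture groups, so the second stage is gated on the first.
- **Primary comparison:** "Shu-Mu-He points group will be compared with Mosapride Citrate tablet group as the primary comparison".
- **Status of the rest:** "comparisons among acupuncture groups will be performed also as exploratory analysis". Shu-Mu versus mosapride and He versus mosapride are not given that label.
- **Discussions section:** the comparison of the three acupuncture groups is said to settle "whether combined use of Shu-Mu-He points will lead to better clinical outcome than using Shu-Mu or He points alone".
- **Planning figures:** the authors "input the four group mean defecation rates as 4.0, 3.8, 5.2, and 2.6 per week". The SD is set at 6.0 in every group, and the resulting effect size is reported as 0.15. The planned size is 175 per group with 15% loss to follow-up. Power for the primary pair is stated at a 1% level, described as making some allowance for multiple comparisons.

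**The concern.** Bonferroni compares every p-value in a family of three with 0.05/3, however the others turn out. Once one hypothesis has been rejected, fewer can still be true, and the remaining p-values need not meet so strict a threshold. Holm uses this without any further assumption. With three groups compared in pairs, logic goes further: if one pair differs, at most one of the other two equalities can still hold. After the first rejection each remaining pair can therefore be tested at the full 0.05, which is Shaffer's version.

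The comparisons affected are the weak ones. The planned differences are 1.4 (Shu-Mu versus mosapride), 1.2 (He versus mosapride), 1.2 (Shu-Mu-He versus Shu-Mu) and 1.4 (Shu-Mu-He versus He), all against an SD of 6.0. They bear on whether the single prescriptions differ from the drug and whether the combination adds anything. Power there is scarce, and the stated method discards some of it for no gain in error control.

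**Working it through.** **Inputs from the article.** Means 4.0 (Shu-Mu), 3.8 (He), 5.2 (Shu-Mu-He) and 2.6 (mosapride); SD 6.0; 175 per group; 15% loss, so 175 × 0.85 = 148.75, about 149 evaluable per group.

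**Assumptions.** Two-sided tests, normal data, pooled variance, two families of three (three groups against mosapride; three pairs among the acupuncture groups), each at 5%.

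**Step 1: reproduce the plan's figures.**
- Effect size: the grand mean is 3.9, and the squared deviations sum to 0.01 + 0.01 + 1.69 + 1.69 = 3.40. Then f = √(3.40/4)/6 = 0.922/6 = 0.154, which agrees with the stated 0.15. With the unrounded f, the omnibus power is 94.0% at 175 per group and 89.6% at 149, in line with the stated 90% after losses.
- Primary pair at 1%: SE = 6√(2/175) = 0.641, and 2.6/0.641 = 4.05. Power ≈ Φ(4.05 − 2.576) = 93.0%, so the claim of over 90% with 175 per group holds.

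**Step 2: power under Bonferroni at 149 per arm.** SE = 6√(2/149) = 0.695. The critical value at 0.05/3 is 2.394.
- Difference 1.2: Φ(1.726 − 2.394) = 25%
- Difference 1.4: Φ(2.014 − 2.394) = 35%
- Difference 2.6: Φ(3.740 − 2.394) = 91%

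With no adjustment at all, the first two would be 41% and 52%. That is the ceiling for any adjusted procedure.

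**Step 3: power under the step-down procedures.** This needs the joint distribution of the tests, so it was simulated (four normal arms, several hundred thousand trials). Holm takes the ordered p-values at 0.05/3, 0.05/2 and 0.05, stopping at the first failure. Shaffer for three pairs takes 0.05/3, then 0.05 and 0.05.

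| Comparison (149 per arm) | Bonferroni | Holm | Shaffer |
|---|---|---|---|
| Shu-Mu vs mosapride | 35% | 44% | n/a |
| He vs mosapride | 25% | 35% | n/a |
| Shu-Mu-He vs mosapride (primary) | 91.0% | 91.4% | n/a |
| Shu-Mu-He vs Shu-Mu | 25% | 27% | 32% |
| Shu-Mu-He vs He | 35% | 37% | 39% |

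Shu-Mu versus He (difference 0.2) stays at about 5% or less under every method.

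**Step 4: error rate.** The first step of Holm and of Shaffer uses the Bonferroni threshold, so when all three groups are equal the chance of any false rejection is the same as under Bonferroni (4.4% in simulation for the acupuncture pairs). When exactly one pair is equal, only that pair can be falsely rejected, and Shaffer never tests it above 5%.

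**Step 5: sensitivity.**
- *Sample size.* With no losses (175 per group), Holm gains 9.5 and 11.1 points for Shu-Mu and He versus mosapride (41% to 51%, 30% to 41%). Shaffer gains 7.8 and 4.8 points for the two Shu-Mu-He pairs.
- *Family.* If all six pairs form one family, Holm gains about 4 points at 149 per arm and about 5 at 175 on the weak comparisons.
- *Gate.* Requiring Shu-Mu-He versus mosapride to be significant at 5% first leaves Bonferroni power for the two acupuncture pairs at 25% and 35%, so the gate does not alter the picture.

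**The case against.** **Bonferroni is valid, so nothing is wrong.** This stands. A reader might infer that the protocol contains an error or risks a false conclusion. It does not: the loss is one of efficiency only. It can still be raised, because the article names the method and an alternative that is never worse for testing costs one sentence.

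**The main inference is untouched.** This also stands. The primary comparison gains under half a point, and the article labels the comparisons among acupuncture groups exploratory. The Discussions section speaks of them more strongly, but that tension is separate from the choice of adjustment.

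**The size depends on procedure and family.** Correct. A reader might infer a uniform loss of 7 to 10 points. The documents do not support that, because the family is not defined and the gain runs from about 2 points (Holm among the acupuncture groups) to about 11 (Holm against control at 175 per group).

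**A three-group F test followed by unadjusted pairs would gain more.** It would: 9.2 and 7.0 points at 149 per arm. But it does not strictly dominate Bonferroni, which rejected a pair that the F-gated test missed in about 0.6% of simulated trials. An F gate also does not suit the skewed and categorical outcomes for which the article plans Kruskal-Wallis and chi-square tests. Holm and Shaffer need only the pairwise p-values.

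**Step-down tests lose the simple simultaneous intervals that go with Bonferroni.** This is a real cost and is dealt with in the fix. It matters more if intervals are to carry the non-inferiority hypothesis in the article's rationale for the acupuncture protocol. The power figures here concern tests of difference only.

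**The detail may lie in the analysis protocol that the article says was developed.** Possibly. If that document already specifies a step-down form, the point falls away. As worded, the article says Bonferroni without qualification.

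**Conclusion.** The point holds as an efficiency improvement, not as a fault in error control. At about 149 per arm, with the plan's means and SD, two-sided tests and families of three, replacing Bonferroni by Holm is worth about 9 and 10 points for Shu-Mu and He versus mosapride. Shaffer's version is worth about 7 and 4 points for Shu-Mu-He versus Shu-Mu and versus He, where plain Holm gives only about 2. The primary comparison is essentially unchanged.

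The change does not rescue the weak comparisons. At 149 per arm they all remain below 50%, because differences of 1.2 to 1.4 are small against an SD of 6.0. That weakness should not be blamed on Bonferroni: even without adjustment power would be only 41% to 52%. The dominance of Holm and Shaffer over Bonferroni does not depend on the family chosen; the number of points gained does.

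**What to change.** Replace the adjustment sentence, before the allocation is unblinded, with: *Within each family, p-values are adjusted by Holm's step-down method; for the three pairwise comparisons among acupuncture groups, Shaffer's version is used (smallest p-value at 0.05/3 and, if that is rejected, the remaining pairs at 0.05).* The families should be named in the same place, since the article leaves them open.

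Cost: one sentence and a few lines of code, with no extra patients and no change in the family-wise error.

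The one real drawback is the intervals. There are two acceptable choices, and the plan should state which is used:
- **Keep Bonferroni-adjusted intervals.** They are simultaneous but will sometimes include zero where the step-down test rejects. For the two Shu-Mu-He pairs this happens in about 32 − 25 = 7% and 39 − 35 = 4% of trials under the planning assumptions.
- **Report ordinary 95% intervals, labelled as unadjusted.** They will sometimes exclude zero where the step-down test does not reject, in about 41 − 32 = 9% and 52 − 39 = 13% of trials for the same pairs.

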## Methods and design

### Design

This is a randomized controlled, four-arm, large-scale trial comparing three acupuncture groups (using different acupuncture points) with Mosapride Citrate control group (Figures 1 and 2). Seven hundred participants will be included from the following eight hospitals: Guang’anMen Hospital of China Academy of Chinese Medical Sciences; First Affiliated Hospital of Chengdu University of Traditional Chinese Medicine (TCM); Affiliated Hospital of Anhui College of TCM; Affiliated Hospital of Changchun University of TCM; Affiliated Hospital of Guangzhou University of TCM; Affiliated Hospital of Hunan University of TCM; Affiliated Hospital of Shandong University of TCM; and Affiliated Hospital of Shanxi College of TCM. These participants will be randomly assigned to four groups (three acupuncture groups and Mosapride Citrate control group) through central randomization in a 1:1:1:1 ratio. The central randomization system will be used and performed by the Clinical Evaluation Center at the China Academy of Chinese Medical Sciences in Beijing. A random number and group assignment will be immediately received by telephone, mobile phone, or website sent from the Clinical Evaluation Center.

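### The plan expects clustering by acupuncturist but only reports an ICC, so the standard error for Shu-Mu-He versus mosapride may be too small

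*Protocol article*

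**What the plan says.** All but the last point below come from the protocol article, section Sample size calculation and statistical analysis.

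- On clustering: "There is one acupuncturist in each center to do all three interventions, which probably introduces clustering effect in this trial". The response, introduced as a consequence of this, is that "we calculated the intracluster correlation coefficient from the results of this trial and report the coefficient".
- On the tests: "Analysis of variance (ANOVA) is used for numerical variables, and Chi-square test for categorical variables". Kruskal-Wallis is named for skewed data and repeated measures analysis for the time points. No centre or acupuncturist term is attached to any of them.
- On sizing: the omnibus power is computed "using a one-way ANOVA fixed effects omnibus test, and assuming a 15% loss to follow-up". The pairwise claim for Shu-Mu-He versus mosapride is over 90% power at the 1% level for a difference of 2.6, SD 6.0 and 175 per group. Neither calculation has a design effect.
- The Design section adds: "Seven hundred participants will be included from the following eight hospitals", allocated "through central randomization in a 1:1:1:1 ratio".

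**The concern.** The article identifies a problem, calls it probable, and offers a remedy that leaves the analysis unchanged. An ICC in the results section tells the reader how strong the clustering was. It does not widen a confidence interval.

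The design makes this matter unevenly. Mosapride is a tablet, so those patients have no acupuncturist. In the primary comparison, a good or poor acupuncturist shifts the Shu-Mu-He patients at that centre and leaves the mosapride patients where they are. With eight acupuncturists, that part of the variation averages over eight units, not 175, and a test that treats patients as independent does not see it. At stake are the true significance level of the primary comparison and the stated power.

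An acupuncturist effect is plausible here. Needle depths are given as ranges, de qi is obtained by hand manipulation, and the current is adjusted between 0.1 and 1.0 mA to patient comfort.

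**Working it through.** **Inputs from the protocol article.** Means 4.0, 3.8, 5.2 and 2.6; SD 6.0; 175 per group; 15% loss; 8 hospitals with one acupuncturist each; primary comparison 5.2 versus 2.6 at 1%.

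**Assumptions.** Two-sided test (sidedness is not stated); equal numbers per centre; normal critical values (z = 2.576 at 1%); an acupuncturist effect in the acupuncture arm only; ICC of 0.01, 0.02 or 0.05. The documents give no ICC, so these values show a range and are not estimates.

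**Step 1: reproduce the stated power without clustering.**
- Omnibus: the mean of the four means is 3.9 and their population SD is 0.922, so f = 0.922/6.0 = 0.154 (the plan: "with a common assumed standard deviation of 6.0, giving a calculated effect size of 0.15"). With 700 × 0.85 = 595 evaluable, noncentral F power at 5% is 89.5%. This agrees with the stated 90%.
- Pairwise: naive SE = 6.0 × √(2/175) = 0.641; 2.6/0.641 = 4.053; power = Φ(4.053 − 2.576) = 93.0%. This agrees with the claim of over 90%.

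**Step 2: add the acupuncturist effect, 175 per arm.**
- Patients per acupuncturist in the Shu-Mu-He arm: m = 175/8 = 21.875.
- Design effect in that arm: DE = 1 + (m − 1) × ICC. It is 1 in the mosapride arm.
- Ratio of true to naive SE: R = √((DE + 1)/2).
- Real level of the naive 1% test: 2 × (1 − Φ(2.576/R)).
- Power at 1% if the true SE is used: Φ(4.053/R − 2.576).

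| ICC | DE | R | Real level of a nominal 1% test | Power at 1% |
|---|---|---|---|---|
| 0 | 1.00 | 1.00 | 1.0% | 93% |
| 0.01 | 1.21 | 1.05 | 1.4% | 90% |
| 0.02 | 1.42 | 1.10 | 1.9% | 87% |
| 0.05 | 2.04 | 1.23 | 3.7% | 76% |

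**Step 3: repeat after 15% loss.** Now n = 148.75 per arm, m = 18.6 and naive SE = 0.696. Power is already down to 88% without clustering. With ICC 0.01, 0.02 and 0.05, R is 1.04, 1.08 and 1.20, and power is 84%, 81% and 71%. These must be read against 88%, not 93%, because the first five points are lost to attrition.

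**Step 4: the other comparisons, by null simulation (4,000 runs per setting, 175 per arm).**
- Effect in the acupuncture arms only: one-way ANOVA across four arms at 5% rejects about 7% at ICC 0.02 and 10.5% at ICC 0.05.
- Shu-Mu-He versus Shu-Mu at 5%: about 4% to 5.5% under the same effect. It is common to both arms and cancels.
- Centre effect shared by all four arms: no inflation. The ANOVA rejects about 5% if allocation is not balanced within centre. If it is balanced, the ratio of true to naive SE is √(1 − ICC), or 0.975 at ICC 0.05, so the test is slightly conservative. Stratification by centre is not stated.

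**The case against.** Four points on the other side deserve weight.

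1. A reader might infer that the plan commits to a one-way ANOVA that ignores centre. It does not. The term one-way appears only in the sizing text; the analysis text says "Analysis of variance (ANOVA) is used for numerical variables" and neither includes nor excludes a centre term. The article also mentions a detailed statistical analysis protocol, which is not shown and could contain one. This stands, so the missing centre term is not in itself the finding. What survives is the ICC sentence: the article states its response to clustering, and that response corrects nothing.

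2. A reader might infer that all the trial's standard errors are wrong. The documents do not support that. Patients are randomised individually, and each acupuncturist delivers all three acupuncture protocols. An effect common to those arms cancels among them, and a centre effect shared by every arm inflates nothing. The naive standard error is too small only for acupuncture versus mosapride, only if acupuncturists differ, and only if inference goes beyond these eight. The last condition is reasonable here: the Discussion section presents the trial as clarifying the efficacy of acupuncture, not the work of eight practitioners.

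3. Training with a qualifying test, and fixed points, frequency and duration, should keep acupuncturists alike. This argues for the lower end of the ICC range. It does not remove the issue, since the plan itself expects clustering despite the training.

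4. The power loss is modest at a small ICC. At 0.01 and 175 per arm, power is about 90%, so the claim is essentially met. This stands too.

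**Conclusion.** The point holds for the primary comparison, in conditional form. The plan calls clustering probable and answers with a descriptive statistic that leaves every standard error as it was. For Shu-Mu-He versus mosapride, if acupuncturists differ and the result is to apply beyond these eight, the naive standard error is too small by 5% to 23% for an ICC of 0.01 to 0.05. A nominal 1% test then runs at 1.4% to 3.7%. Power at 175 per arm falls from 93% to between 90% and 76%; after 15% loss it falls from 88% to between 84% and 71%. All of this rests on the assumed ICC, eight equal centres and normal critical values. Nothing in the documents shows which ICC applies. The exploratory comparisons among the acupuncture arms are not inflated by a common acupuncturist effect.

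**What to change.** 1. Include centre, which here is the same as acupuncturist, in the primary outcome model.
2. For acupuncture versus mosapride, also report an analysis that lets the effect vary by centre: a mixed model with an acupuncturist random effect in the acupuncture arms only and small-sample degrees of freedom. Take the reported ICC from that model.
3. State that the power of over 90% assumes no clustering.

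A centre term alone does not account for acupuncturists who differ; it gives an answer for these eight centres. The second analysis is the one that addresses the clustering the plan expects.

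**Cost.** The change is to analysis wording and uses centre, which a multicentre trial already records. The real price is a wider interval for acupuncture versus mosapride, possibly noticeably so with only eight clusters. In the conservative limit of 7 degrees of freedom (an assumption; the method used may give more), the 1% critical value rises from 2.58 to 3.50. Noncentral t power at 148.75 per arm would then be about 57%, 53% or 43% for ICC 0.01, 0.02 or 0.05. It is therefore defensible to keep the centre-adjusted model as primary and name the random-effect model as a sensitivity analysis, provided this is fixed before outcome data are analysed.
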